## Abstract

**Background:**

Recent theoretical models emphasize the role of impulsive processes in alcohol addiction, which can be retrained with computerized Cognitive Bias Modification (CBM) training. In this study, the focus is on action tendencies that are activated relatively automatically.

**Objective:**

The aim of the study is to examine the effectiveness of online CBM Alcohol Avoidance Training using an adapted Approach-Avoidance Task as a supplement to treatment as usual (TAU) in an outpatient treatment setting.

**Methods:**

The effectiveness of 8 online sessions of CBM Alcohol Avoidance Training added to TAU is tested in a double-blind, randomized controlled trial with pre- and postassessments, plus follow-up assessments after 3 and 6 months. Participants are adult patients (age 18 years or over) currently following Web-based or face-to-face TAU to reduce or stop drinking. These patients are randomly assigned to a CBM Alcohol Avoidance or a placebo training. The primary outcome measure is a reduction in alcohol consumption. We hypothesize that TAU + CBM will result in up to a 13-percentage point incremental effect in the number of patients reaching the safe drinking guidelines compared to TAU + placebo CBM. Secondary outcome measures include an improvement in health status and a decrease in depression, anxiety, stress, and possible mediation by the change in approach bias. Finally, patients’ adherence, acceptability, and credibility will be examined.

**Results:**

The trial was funded in 2014 and is currently in the active participant recruitment phase (since May 2015). Enrolment will be completed in 2019. First results are expected to be submitted for publication in 2020.

**Conclusions:**

The main purpose of this study is to increase our knowledge about the added value of online Alcohol Avoidance Training as a supplement to TAU in an outpatient treatment setting. If the added effectiveness of the training is proven, the next step could be to incorporate the intervention into current treatment.

**Trial Registration:**

Netherlands Trial Register NTR5087; http://www.trialregister.nl/trialreg/admin/rctview.asp?TC=5087 (Archived at WebCite http://www.webcitation.org/6wuS4i1tH)

## Introduction

### Background

Alcohol misuse is a key public health concern and is associated with a high burden of disease, which in turn contributes to considerable economic costs for both individuals and society [1]. Although addicted people are aware of the negative consequences, most continue this self-destructive behavior. This paradox can be explained by models that conceptualize addictive behavior as a “dual process”: an imbalance between relatively automatic processes and conscious/cognitive processes [2].

Recent research provides evidence that addictive behaviors are partly guided by relatively automatic processes that occur outside conscious control, making the individual respond impulsively to cues associated with the addictive substance, rather than displaying inhibitory control [3,4]. Multiple implicit cognitive biases have been shown to play a role in alcohol addiction, such as an attentional bias for alcohol-related stimuli [5], a memory bias for the automatic activation of alcohol-related associations [6], and a bias toward automatically activated action tendencies to approach alcohol [7].

Cognitive behavioral therapy (CBT) is an evidence-based treatment for a variety of disorders including alcohol use disorders. Various meta-analyses show a large effect size in treatment outcomes of patients with alcohol disorders compared to no treatment and a small but clinically significant effect when compared to other active treatments [8,9]. Although effective, CBT programs primarily target the reflective, voluntary system and leave the automatic, impulsive system mostly unaffected [10,11]. This suggests that treatment of alcohol use disorder could be improved by also focusing on those processes that are primarily automatic. Over the past decade, a set of computerized training programs have been developed with the aim of reducing automatic biases in information processing and thereby reducing psychopathology. Collectively, these programs are termed Cognitive Bias Modification (CBM) training [12-15]. Alcohol-related CBM programs have been shown to be effective in changing attentional bias [16-18], memory bias [19,20], and approach bias [21-23], which in turn is often associated with reductions in drinking behavior or reduced relapse into drinking behavior.

The current study focuses on retraining the automatically triggered behavioral tendency to approach alcohol, by using online Alcohol Avoidance Training. In a preliminary test with this CBM training among heavily drinking students, it was shown to be successful in modifying the automatic action tendencies and related memory associations, and students who were successfully trained to avoid alcohol drank less alcohol in a taste test directly after the training [22]. The first clinical trials with German alcohol-dependent inpatients showed that this training reversed the patients’ approach bias into an avoidance bias for alcohol with generalization of the training effects to other experimental tasks [21].

More importantly, compared to patients in the placebo condition, patients in the training condition showed significantly less relapse after a year. A second study in the same clinic replicated the main findings and showed that the effects on relapse were mediated by change in approach bias [23]. While these studies tested the added effect of CBM training on top of treatment as usual (TAU), recent studies examined the effect of the training as a stand-alone intervention and failed to observe positive training effects [24,25].

Because TAU for alcohol use disorders often comprises of outpatient treatment, it is relevant to study the added value of CBM outside the clinical setting. Effectiveness of CBM in an outpatient setting may be attenuated by a lower adherence as compared to an inpatient setting. However, offering CBM online at home seems to generate high adherence rates. Combining Internet-based CBM with Internet-based CBT was found to be an acceptable form of treatment delivery for patients with depression, showing full adherence to the seven CBM sessions by 81% of participants [26]. Similarly, Salemink and colleagues showed an adherence rate of 85% among patients with different anxiety disorders, completing all 8 online training sessions (45 min each) in a period of 11 days [27]. Delivering CBM online in an outpatient setting may even generate stronger effects than in a clinical setting. There is preliminary evidence that training in a relevant context improves the effectiveness of CBM training. Kuckertz et al [28] showed improved results for CBM training in anxiety patients when patients were in a state increased anxiety while undergoing the CBM training. In case of alcohol addiction, training in a relevant, real-life context might lead to better results.

We, therefore, are interested in whether the positive added effects found in clinical inpatient samples [21] with the CBM training on local desktop computers in the clinic is possible to reproduce when the CBM is administered online in an outpatient sample.

### Aims and Hypotheses

The aim of the current study is to investigate the effectiveness of online CBM Alcohol Avoidance Training as an adjunct to TAU in an outpatient treatment setting. Patients receive eight sessions of either the active or placebo version of the CBM Alcohol Avoidance Training during their TAU. The primary goal is to test the effects of this adjunct CBM on alcohol use immediately after finishing the intervention and three and six months later, by looking at the changes in the level of alcohol consumption over a week. The primary outcome measure is the percentage of the patients reaching the low-risk drinking level, defined as <22 standard units/week for men and <15 for women [29]. It is expected that more patients in the experimental condition will reach low-risk drinking level. Furthermore, it is hypothesized that the CBM intervention decreases or reverses the approach bias, and these changes are expected to mediate the effects on alcohol use [23]. An improvement in health status and a decrease in depression, anxiety and stress for patients in the training condition, compared to the placebo condition, are expected as secondary outcomes. To investigate who benefits most from the training, possible moderators will be examined. Automatic impulses may be controlled by cognitive capacity available to inhibit these impulses. Refusal self-efficacy is considered such a cognitive resource. Following this assumption, CBM interventions can yield benefits, especially for those with a relatively weak cognitive control over their impulses to drink [12,30-32]. In line with the predictions from dual process models and prior CBM trials [12], it is expected that for patients with a low baseline self-efficacy, the additional effect of the Alcohol Avoidance Training will be stronger. Similarly, time-varying self-efficacy is expected to partially mediate the CBM effect as repeated experiences of successful coping due to stronger avoidance responses will enhance refusal self-efficacy. Patients’ adherence and perceptions of treatment acceptability, and credibility will also be examined.

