### Participants and Procedure

The study population consists of patients aged 18 years or older with a primary alcohol problem, who are currently following TAU at Tactus Addiction Treatment Institute in the Netherlands. One general inclusion criterion is accessibility and ability to use the Internet, since patients will need to access CBM-training online. Two exclusion criteria apply for the TAU: (1) serious psychiatric illness with a risk to decompensate while decreasing alcohol consumption; and (2) the possibility of severe physical illness as a consequence of decreased alcohol consumption. There are no additional criteria for participation in this study.

Patients for the training are recruited by therapists at Tactus Addiction Treatment Institute. After the regular intake procedure, including baseline questionnaires, the TAU starts. Before the patient reaches the goal-setting assignment, the therapist will inform the patient about the CBM training and provide the patient with further information about the study. If the patient wants to participate, an informed consent form will be provided to patients by the therapist. After signing the form, the patient receives login credentials for the CBM training from the researcher.

After finishing registration, the patient is randomly assigned to the Alcohol Avoidance Training or to the placebo training, and receives an email with a link to the CBM training website. After logging in, the patient receives instructions about the training. At the start of each session, the patient is asked to complete the additional questionnaires for the purpose of this study, consisting of self-reported weekly alcohol consumption and desire for drinking. Each of the eight training session takes about 10-15 min. The first training session is preceded by an (online) preassessment and the final training session is followed by an (online) postassessment. Three and six months after the postassessment, each patient will receive online follow-up questionnaires. In case of nonresponse, the patient will be reminded by email or phone to complete the questionnaire.

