### Measures

An overview of all measurements instruments along with the randomized controlled trial measurement time-points are presented in Table 2.

Demographic characteristics like gender, age, educational level, employment and clinical case history details (duration of alcohol dependence, previous detoxifications and treatments, duration of current abstinence and medication intake) will be collected during the baseline assessment of the TAU.

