#### Self-Efficacy

Using eight items of the Drinking Refusal Self-efficacy Questionnaire (DRSEQ), participants will be asked whether they feel sure they can refuse alcohol on the three subdimensions of self-efficacy: social pressure, emotional relief and opportunism [48].

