**Baseline measures**												
	Demographics	✓										
	MAP-HSS	✓								✓		✓
	DASS	✓								✓		✓
	OCDS	✓								✓		✓
	DMQ-R			✓								
	CIDI	✓										
	Drinking refusal self-efficacy	✓										

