### Statistical Analyses

Analyses will be conducted in agreement with intention-to-treat principle. Missing data points will be handled using multiple imputation [53]. One-way ANOVAs and χ²-tests will be performed to see if there are any significant differences at baseline between the two CBM training conditions (Avoid Alcohol vs placebo) for any of the demographic variables or outcome measures. Nonsignificant differences will indicate successful randomization. To determine the primary outcome, a logistic regression analysis will be used to test the differences in the proportion of patients reaching the low-risk drinking criterion between the CBM Alcohol Avoidance Training and CBM placebo condition, both at posttest and at follow-up. If necessary, baseline confounders will be controlled for, and significant interaction effects will be further investigated using post hoc *t*-tests (independent samples *t*-test and paired samples *t*-test). Effect sizes on clinically relevant outcomes at postintervention and follow-up will be calculated by Cohen’s d using the means and pooled standard deviations of the measurements of the conditions. Effect sizes of .56-1.2 are considered large, .33-.55 are considered moderate, and less than .33 are considered small [54]. Repeated measures ANOVAs will be conducted to test for differences between the CBM Alcohol Avoidance Training and the CBM placebo condition on the secondary outcomes general health condition, depression, anxiety and stress. Mediation analyses will be conducted by applying the analytic procedure according to Preacher and Hayes [55] and Hayes [56] to examine whether a change in approach bias is mediating the Alcohol Avoidance Training effects on our primary outcome measure. Logistic regression analyses will be used to assess whether patient characteristics moderate the effect of the Alcohol Avoidance Training on our primary outcome measure. The procedure proposed by Baron and Kenny [57] will be adopted. Descriptive statistics will be used to investigate to what extent patients adhered to the Alcohol Avoidance Training (in terms of timing, frequency, and duration of sessions) and to what extent patients found the Alcohol Avoidance Training both acceptable and credible (testing adherence, acceptability, credibility).

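### Refusal self-efficacy is hypothesised as a time-varying mediator, but the published schedule measures it only once, before randomisation

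*Protocol article*

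**What the plan says.** The Aims and Hypotheses section makes two different predictions about refusal self-efficacy.

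- **Moderation:** "it is expected that for patients with a low baseline self-efficacy, the additional effect of the Alcohol Avoidance Training will be stronger".
- **Mediation:** "time-varying self-efficacy is expected to partially mediate the CBM effect", on the reasoning that "repeated experiences of successful coping due to stronger avoidance responses will enhance refusal self-efficacy".

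The Measures section introduces the schedule with "An overview of all measurements instruments along with the randomized controlled trial measurement time-points are presented in Table 2". In that table the row "Drinking refusal self-efficacy" stands in the block of baseline measures and has one tick, under the TAU baseline. MAP-HSS, DASS and OCDS, in the same block, are also ticked at the TAU posttest and at follow-up.

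The Self-Efficacy paragraph describes the instrument without giving a time point: "Using eight items of the Drinking Refusal Self-efficacy Questionnaire (DRSEQ), participants will be asked whether they feel sure they can refuse alcohol". The Statistical Analyses section plans a mediation analysis "to examine whether a change in approach bias is mediating the Alcohol Avoidance Training effects on our primary outcome measure" and mentions no other mediator.

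**The concern.** A mediator has to be something that the randomised intervention can change. The mediation hypothesis says that training raises refusal self-efficacy and that this rise carries part of the effect on drinking. Self-efficacy therefore has to be observed after training has started. On the published schedule it is observed only before allocation.

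At stake is one of the trial's stated mechanism hypotheses. If the schedule is followed as printed, the hypothesis will either disappear from the report without explanation or be addressed with a baseline score that cannot answer it. Once data collection closes, the missing measurements cannot be recovered.

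**Working it through.** There is no figure in the plan to recompute for this point. The check sets the hypotheses against the schedule.

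**1. What the mediation hypothesis requires.** Let A be the arm, M0 self-efficacy before randomisation, M1 self-efficacy after training has begun, and Y reaching the low-risk drinking criterion. A minimal mediation model is

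- M1 = i + a·A + c·M0 + error
- logit P(Y = 1) = j + c′·A + b·M1 + d·M0

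The indirect effect, on the log-odds scale, is a × b. Both equations need M1.

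**2. The order of events.** From Participants and Procedure: intake with baseline questionnaires, start of TAU, information and consent, registration, randomisation, preassessment, eight training sessions, postassessment, then follow-up at 3 and 6 months. The TAU baseline thus precedes randomisation.

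**3. What is scheduled.**

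| Hypothesis | Value needed | Scheduled in Table 2? |
|---|---|---|
| Baseline self-efficacy moderates the effect | M0 | Yes, at the TAU baseline |
| Time-varying self-efficacy mediates the effect | M1 (with M0 for adjustment) | No |

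Self-efficacy measurements in total: 1. After randomisation: 1 − 1 = 0.

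**4. The consequence.** Without M1 neither equation can be fitted, and no increase in sample size changes that. Putting M0 in place of M1 does not help. Because M0 is recorded before allocation, randomisation gives E(M0 | A = 1) = E(M0 | A = 0). Hence a = 0 by design and a × b = 0, whatever the true mechanism. Any observed difference in M0 between arms would be chance imbalance.

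**5. Whether another part of the article fills the gap.**

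- The questionnaires at the start of each training session are described in Participants and Procedure as "consisting of self-reported weekly alcohol consumption and desire for drinking". Self-efficacy is not among them.
- The Self-Efficacy paragraph mentions no repeat.
- Primary and Secondary Outcome Measures names change in approach bias as the mediator and does not mention self-efficacy.
- Statistical Analyses does the same.

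**6. What is not affected.** The 152 patients per condition relate to the primary comparison (68% against 81%, one-sided alpha 0.05, Fisher's exact test). That figure reproduces: exact power is 0.7999 with 151 per arm and 0.8030 with 152. It has no bearing on this point.

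**The case against.** The strongest reply is that the missing ticks may be a reporting slip. Table 2 as read is not tidy: one tick sits on the heading row for secondary outcomes, which is not an instrument. The block of baseline measures contains three scales that are repeated later, so the block label does not prove collection at baseline only. The DASS paragraph speaks of measurement at baseline, yet the table repeats that scale and the analysis treats it as an outcome. The phrase about time-varying self-efficacy itself suggests that repeated measurement was intended. A fuller protocol, not shown, might contain it, and details of a mediation model may properly be left to the analysis plan.

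Parts of this stand. The finding concerns the schedule as published, not what may be done in practice. The silence of the analysis section about a self-efficacy mediator carries little weight alone. The hypothesis is also ancillary: it is a single prediction in the aims and does not appear in the abstract or among the secondary outcomes.

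The rest does not remove the problem. Three neighbouring rows keep their later ticks, so loss from the self-efficacy row alone is unlikely. For the DASS, the table supplies the time points that the prose leaves out; for the DRSEQ, neither table nor prose does. This is a conflict between a stated hypothesis and a stated schedule that is presented as complete, and an analysis plan cannot supply data that were not collected.

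**Conclusion.** The concern holds. On the schedule as published, self-efficacy has one pre-randomisation measurement and none afterwards, so mediation by time-varying self-efficacy cannot be tested. The conclusion assumes that Table 2 is complete, as the Measures section presents it, and that its ticks were read correctly.

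The consequence is limited to one ancillary mechanism hypothesis. The primary outcome, the sample size, the approach-bias mediation analysis and the moderator hypothesis for baseline self-efficacy are unaffected. The plan should nevertheless be corrected, because the gap becomes permanent when collection ends. The article reports that recruitment was active, with enrolment to be completed in 2019, so a remedy was still open when it was written.

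**What to change.** Reconcile Aims and Hypotheses, Table 2 and Statistical Analyses in one of these ways.

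1. **Keep the hypothesis and collect the data.** Add the eight DRSEQ items to the online postassessment and to the 3- and 6-month questionnaires, and tick those columns in Table 2. Name self-efficacy at postassessment, adjusted for its baseline value, as a mediator of the follow-up outcome. The follow-up outcome is the suitable one because consumption at postassessment refers to the previous week and so precedes the self-efficacy rating.
2. **Withdraw the hypothesis.** Delete the mediation sentence and keep baseline self-efficacy as a moderator only.
3. **If the DRSEQ is already repeated,** correct Table 2 and add self-efficacy to the mediation paragraph.

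The first option costs eight items at assessments that already exist, and a slight burden on patients. Its real limitation is that recruitment began in May 2015, so everyone already past postassessment would lack the mediator, with missingness tied to calendar time. The mediation analysis should then be confined to patients, in both arms, who reach postassessment after the items are introduced. The values for earlier patients should not be imputed. The analysis will be less precise, and the report should say so. The second option costs only the hypothesis and is the minimum correction.

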## Methods

### Trial Design

This study is a double-blind randomized placebo-controlled trial in a real-world setting. Patients receive TAU, consisting of outpatient personalized care

All patients with a primary alcohol problem enrolled for TAU are invited by their therapist to participate in the Alcohol Avoidance Training. After giving informed consent, patients are randomly assigned to one of the two training conditions: CBM Alcohol Avoidance Training or CBM placebo training. Patients begin the training simultaneously with the start of the behavioral change part of their treatment. Patients are recommended to follow a 15-minute CBM session twice a week for a period of five weeks. The CBM training includes eight sessions, preceded and followed by an assessment session, the preassessment and postassessment, respectively. Patients will be rewarded with a € 20 voucher if they complete all ten sessions. Three and six months after the TAU there will be follow-up assessments. Figure 1 shows the participant flow chart of the study.

The study has been approved by the Ethics Committee of Amsterdam Academic Medical Centre in January 2015 (reference number 2014_154#C20141463) and has been registered at the Netherlands Trial Register (NTR5087).

